### 2.2 Target trials and target estimand

To make the aims of our study as clear as possible we formulate multiple *target trials*, as proposed by Hernán and Robins (22). A target trial is a description of a hypothetical study that we, the investigators, would conduct if there were no ethical or practical limitations on what we could do. It should include a description of all relevant study characteristics, such as inclusion- and exclusion criteria, a clear definition of the population of interest and how the study would be conducted. The aim is then to *emulate* these trials using available data and appropriate analysis techniques (22). This framework makes it easier to follow the International Council for Harmonization of Technical Requirements for Pharmaceuticals for Human Use guidelines (ICH-E9) for defining target estimands (25, 26) and allows us to formulate a clear definition of the time of inclusion of each patient (“time zero”) (27). Similar studies concerned with COVID-19 vaccine effectiveness have also used this approach effectively (28). Table 1 summarizes the most important components of the respective target trial protocols.

**Table 1 T1:** A summary of the most important protocol components for each of the planned target trial emulations.

**Protocol component**	**Target trial**	**Emulation with observational data**
Data Source	Prospectively collected data between 2013 and 2021.	Routinely collected claims data from a large German statutory health insurance company (BARMER) from 2013 to 2021.
Eligibility Criteria	(1) ≥ 18 years old (2) Biological sex of either male or female (3) No organ transplantation in the past 2 years (4) No cancer in the past 2 years (5) No autoimmune-related disease other than MS, IBD, or CIRD in the past 2 years (6a) For the herpes zoster trial: No previous herpes zoster vaccination (6b) For the influenza trials: No previous influenza vaccination in the current influenza season	Same as in the target trial, but with one additional criteria: (7) Enrollment in the BARMER health insurance company for ≥ 2 years with interruptions of no more than 5% of the total time
Treatment Strategies	(a) Vaccination against herpes zoster infection at treatment assignment with another vaccination between two and six months afterwards (b) Vaccination against influenza infection at treatment assignment (c) No vaccination at treatment assignment (no placebo) Treatment strategies (a) and (b) are compared to (c) in their separate trials.	

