#### 2.5.2 Treatments

The “treatments” in this study are the two different types of vaccines of interest. We will not differentiate between different subtypes of vaccines in the influenza vaccine effectiveness trials. Any vaccine against influenza will be considered an “influenza vaccine”, regardless of its' underlying mechanism and irrespective of which company created the vaccine. In the herpes zoster trial we will only consider the inactivated recombinant zoster vaccine (Shringrix^®^) (41). In Germany, vaccinations are usually provided by physicians in primary care. Physicians receive a reimbursement for each vaccination from the statutory health insurance of the individual being vaccinated. To this end, a standardized reimbursement code [German: Gebührenordnungsposition (GOP)] is used and transferred to the insurance as part of a reimbursement claim. We will use these codes to identify vaccinations in our study population, using both codes applying uniformly for all regions in Germany and codes only used for specific regions and time periods. The reimbursement codes used are listed in the online supplement.

There is, however, one special case that needs to be mentioned. Whenever individuals get vaccinated through a company physician (in German: Betriebsärzte), the reimbursement code is not transferred to the insurance company of the individual. The reimbursement is instead taken care of by the companies themselves. Additionally, a few pharmacies and hospitals also vaccinate individuals without sending reimbursement codes to the insurance company (42). Because these vaccinations never show up in the individuals data of the health insurance, the vaccination status of these individuals will be misclassified in the analysis. We expect this issue to have a minor impact, because the majority of vaccinations are performed by primary care physicians in Germany. There is currently no official data available to quantify the proportion of vaccinations performed in these different settings. Due to the complex nature of the proposed analysis strategy, as described in Section 2.6, it is also not possible to apply standard methods of quantitative bias analysis to quantify the effects of this potential bias (43). To still get a rough estimate of the potential impact of this misclassification, we will repeat the main analysis after removing 10% of all vaccination dates from the available data in a sensitivity analysis.

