#### 2.6.3 Intercurrent events

Four possible types of events that may happen to individuals after inclusion into the study need to be accounted for. These possibly events are:

Death.Loss to follow-up.Individuals receiving another unplanned vaccination after the first dose (e.g., non-adherence to the “assigned” treatment status).Individuals *not* receiving a planned second vaccination (only applicable to the herpes zoster vaccine effectiveness study).

Of course, death may occur at any time for any number of reasons, while loss to follow-up may only occur when individuals terminate their enrollment in the BARMER health insurance company. The third type of intercurrent event requires more considerations. In practice, individuals may receive another vaccination after already having received the recommended amount of doses. Additionally, because only information at the time of inclusion is used when performing the matching, it is possible that individuals which were selected as controls get vaccinated themselves during follow-up. Lastly, because the matching is performed on the date of first vaccination, it is possible that individuals do not receive a planned second vaccination as recommenced for herpes zoster vaccines.

In all analyses, individuals will be considered right-censored at their time of loss to follow-up or death (whichever occurs first). In the primary *per-protocol* analysis, the event time of individuals will also be censored at the time at which they receive a vaccination that does not correspond to the planned treatment strategy, or at the time at which they should have received a second vaccination but did not do so. This way, only time during which the individuals adhered to their assigned treatment is considered in the analysis. This strategy likely results in covariate-dependent censoring, which will be accounted for by also censoring the matched pair of the individual at the same time (56). In the secondary *intention-to-treat* analysis, the subsequent vaccinations are ignored instead, which results in all potential effects of non-adherence to the assigned treatment to be included in the analysis.

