## 3 Discussion

The proposed study has multiple strengths. One of the biggest strengths is its large sample size. With approximately 50,000 MS patients, 300,000 CIRD patients, 80,000 IBD patients and potentially millions of control patients, this study is, to the best of our knowledge, the largest of its kind. Because it is based on data from a German health insurance provider, it also contains information on the medications prescribed to each patient, as well as their acquired infections and comorbidities. This large sample size makes a detailed disease specific population based comparison of the vaccine effectiveness with appropriate controls possible. The available information also makes adjustment for many of the relevant confounders feasible. The very limited amount of inclusion criteria additionally facilitates the generalizability of the obtained results.

A limitation of this study is the potential of unmeasured or unknown confounding. As discussed earlier, we are not able to adjust for all confounders that were identified by our assumptions about the causal data generation process. For example, it is impossible to measure social contact behavior from the available data. It is also possible, if not likely, that the DAG we specified is partially wrong or fails to include other, currently unknown, confounders. This is a frequent problem in observational studies, although it is not always acknowledged (32). We will attempt to quantify the impact of this potential source of bias through pre-planned sensitivity analyses.

A further limitation is the potential of misclassification of the vaccination status due to individuals getting vaccinated through their company physicians, or in rarer cases in hospitals or pharmacies. Because some individuals will be misclassified as “unvaccinated,” it is possible that the estimates of the vaccine effectiveness will be biased downwards. However, we expect this to be a minor issue, because most individuals in Germany get vaccinated through their primary care physician. Under the assumption that the misclassification rate does not differ between the considered disease groups, we would also not expect bias of the contrast between the vaccine effectiveness estimates.

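### In the zoster trial, removing 10% of vaccination dates does not cleanly mimic vaccinated people who appear unvaccinated; the deletion unit should be the person

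*Protocol article*

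**What the plan says.** Section 2.5.2 explains that vaccinations given by company physicians, and by a few pharmacies and hospitals, generate no claim to the insurer. As a result "the vaccination status of these individuals will be misclassified in the analysis". The Discussion (Section 3) gives the direction: because some vaccinees count as unvaccinated, "it is possible that the estimates of the vaccine effectiveness will be biased downwards". Section 2.5.2 adds that no official data show how vaccinations divide between settings and that standard quantitative bias analysis cannot be applied. The planned substitute, offered as a rough estimate, is: "we will repeat the main analysis after removing 10% of all vaccination dates from the available data in a sensitivity analysis".

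The same sentence covers both vaccines, but the strategies in Table 1 (Section 2.2) differ:

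- Zoster: "Vaccination against herpes zoster infection at treatment assignment with another vaccination between two and six months afterwards".
- Influenza: "Vaccination against influenza infection at treatment assignment".

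Three further rules bear on the zoster trial:

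- Section 2.3 excludes anyone with an earlier zoster vaccination.
- Time zero is the first dose, "because the matching is performed on the date of first vaccination" (Section 2.6.3).
- The primary per-protocol analysis censors a vaccinee when a due second dose has not been received, and censors the matched partner at the same time (Section 2.6.3).

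**The concern.** The bias is described for persons, while the check is defined for dates. With one dose per season the two units hide the same people. With two doses they do not, because eligibility, time zero and per-protocol censoring all depend on which doses are on record.

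Deleting one zoster date from a completer has one of two effects:

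- **Only dose 1 removed.** The person looks unvaccinated from the true dose 1 until dose 2 and can be drawn as a control in that window. Dose 2 then passes as a first dose, sets a time zero two to six months late, and is followed by an apparent missed second dose.
- **Only dose 2 removed.** The person stays in the vaccinated arm from the right date but looks like a non-completer and is censored with the partner. No control is contaminated.

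This rerun is the only quantitative check of exposure misclassification that the article plans. If its result mixes hidden vaccinees, shifted start dates and added censoring, the reader cannot tell which of them moved the estimate, or whether they offset one another.

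**Working it through.** The article derives no figure on this point; the 10% is a chosen setting. There is nothing to reproduce first.

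**Inputs.** Deletion rate d = 0.10 per date (Section 2.5.2). Two doses per zoster completer, two to six months apart (Table 1). One dose per influenza season (Table 1). Assumption: dates are removed at random and independently of the person.

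**Step 1: two-dose completers, independent deletion**

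| Dates removed | Formula | Share | How the person then appears |
|---|---|---|---|
| Both | d² = 0.1 × 0.1 | 1% | never vaccinated |
| Dose 1 only | d(1−d) = 0.1 × 0.9 | 9% | unvaccinated until dose 2, then false time zero and false missed second dose |
| Dose 2 only | (1−d)d = 0.9 × 0.1 | 9% | correct time zero, false missed second dose |
| Neither | (1−d)² = 0.9 × 0.9 | 81% | unchanged |

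A simulation of 1,000,000 completers with exactly 10% of dates removed gave 0.99%, 9.01%, 9.01% and 80.99%.

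- Hidden at the true time zero: 1% + 9% = 10%.
- Hidden for the whole of follow-up: 1%.
- False missed second dose: 9% + 9% = 18%. Among completers still seen as vaccinated this is 18/99 = 18.2%, and a false time zero affects 9/99 = 9.1%.

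**Step 2: duration.** In the per-protocol analysis, a control whose dose 1 was deleted is censored at the recorded dose 2. That contamination lasts at most two to six months, in a trial that runs for 37 months (December 2018 to December 2021: 1 + 36).

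**Step 3: deletion by person.** Removing all zoster dates of 10% of vaccinees hides 10% of completers permanently, with 0% false time zeros and 0% false missed second doses. Independent date deletion would need d = √0.10 ≈ 31.6% to hide as many permanently.

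**Step 4: sensitivity to the assumptions.** Let a person's two deletions have correlation ρ (not given in the article). Then P(both) = d² + ρd(1−d), and the share with a false missed second dose is 2[d − P(both)].

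| ρ | Permanently hidden | False missed second dose |
|---|---|---|
| 0 | 1% | 18% |
| 0.25 | 3.3% | 13.5% |
| 0.5 | 5.5% | 9% |
| 0.75 | 7.8% | 4.5% |
| 1 | 10% | 0% |

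One-dose vaccinees are hidden at 10% under either unit. If they make up a share s of zoster vaccinees (assumed 10% to 50%), the permanently hidden share of all vaccinees under independent date deletion is (1−s)(0.01) + s(0.10), which is 1.9% to 5.5%.

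**Step 5: rough effect on vaccine effectiveness (VE).** With coverage c (assumed) and permanently hidden fraction h, the share of true vaccinees in the apparently unvaccinated pool is hc/(1 − c + hc).

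| c | By date (h = 0.01) | By person (h = 0.10) |
|---|---|---|
| 5% | 0.05% | 0.52% |
| 10% | 0.11% | 1.10% |
| 20% | 0.25% | 2.44% |

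If true VE is 70% (assumed) and the pool share is q, the observed relative risk is about 0.300/(1 − 0.7q). At q = 0.011 it is 0.302, and VE falls by about 0.2 points. At q = 0.024 it is 0.305, and VE falls by about 0.5 points. This covers contamination of the control pool only. The effects of false time zeros and added censoring have not been quantified.

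**The case against.** The strongest reply has four parts.

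1. **The gap can be read per vaccination.** Section 2.5.2 says that certain vaccinations go unrecorded, and it does not say that a person's two doses share a setting. Someone with one dose in hospital and one in primary care really would have a partial record. This stands: false first doses and false non-completion may be genuine forms of the error. It argues for a separate single-dose scenario, not for merging the two.
2. **The sampling mechanics are unstated.** A condensed article may leave them elsewhere, and the 1/9/9/81 split depends on independence. This also stands, and Step 4 gives the range. Still, the article does name the unit, and that unit is dates.
3. **The effect may be small.** Section 2.6.1 expects only a relatively small proportion to be vaccinated, and the rough figures are 0.2 to 0.5 points even under deletion by person. This lowers the priority. It does not make the planned rerun interpretable.
4. **The extra censoring is contained.** The partner is censored as well, so the main effect of a deleted dose 2 is lost follow-up, and the intention-to-treat analysis is untouched by it. This is correct, but the primary analysis is per-protocol, and the 9% with a false time zero remain in both.

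A reader might infer that only about 1% misclassification is tested for zoster. The documents do not support that: 10% of completers are hidden at their true first dose and can be drawn as controls until dose 2, and one-dose vaccinees are hidden at the full 10%.

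**Conclusion.** The concern holds in a limited form. For the two-dose zoster trial, the date-level rule does not cleanly represent vaccinated people appearing unvaccinated. Under random, independent deletion, 10% of completers are hidden at their true time zero but only about 1% throughout, and about 18% acquire a false missed second dose that triggers censoring of the pair in the primary analysis. These figures rest on independence, which the article does not state, and they apply to completers only. If both dates of a person were always removed together, the problem would disappear.

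A reader might also infer that the rerun gives false reassurance or biases the zoster result materially. Neither is shown: the net effect on VE has not been estimated, and the main analysis is not altered. What is established is that a shift, or no shift, could not be attributed to misclassification. Within a single-dose influenza season, deletion by date and by person hide the same 10% of vaccinees, so the exposure is not affected in this way. Priority is low.

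**What to change.** In Section 2.5.2, state the deletion unit. For the zoster trial, remove all zoster vaccination dates of a random 10% of vaccinated individuals. For the influenza trials, date-level deletion within a season can stay. If partial records from doses given in different settings are of interest, run single-dose deletion as a separate, labelled scenario and report it apart from the person-level result.

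The cost is one or two sentences of text and a change of sampling unit in the code. No further data are needed, and the main analysis is unchanged.

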#### 2.5.3 Outcomes

Different outcomes will be used for each of the considered vaccine effectiveness trials. For the emulation of the proposed target trials, the date on which the respective outcomes occurred is required. Our aim is therefore to identify this date of occurrence given the available insurance claims data. In the German system, ICD-10 codes that were used in the inpatient setting are directly associated with an exact date. Outpatient ICD-10 diagnosis, however, are only associated with a time interval which may be up to 91 days (one quarter) long, depending on the patient. In some cases, the corresponding date of the diagnosis must therefore be identified using associated treatments or doctors certificates on the incapacity to work, for which exact dates are available. The concrete strategy used to identify the dates for outpatient diagnosis of each defined outcome and associated sensitivity analyses are described in the online supplement.

The outcome for the herpes zoster vaccine effectiveness analysis is a *medically attended herpes zoster infection*. This outcome will be identified from the available data through the use of ICD-10 code **B02** (inpatient or outpatient diagnosis), in conjunction with a prescription for an antiviral drug (acyclovir, valacyclovir, famciclovir, or brivudin). This is similar to the definition proposed by Zerbo et al. (44), which was estimated to have a positive predictive value of 96.7% by the same authors. Other studies additionally employed information about positive laboratory tests (45), which is not possible in this study due to a lack of available data.

For the influenza vaccine trials we will use *medically attended influenza* as the primary outcome, as recommenced in the literature (30, 46). We define a medically attended influenza as an influenza infection that results in any type of formal contact between the patient and a health care professional. In particular, we define a medically attended influenza infection as having occurred when either one of the ICD-Codes **J09**, **J10**, or **J11** has been used as a secured outpatient diagnosis or in an inpatient main or secondary diagnosis. The medically attended influenza is considered to be *severe* if it is associated with a hospital admission due to pneumonia or death. We will use the severe medically attended influenza as a secondary outcome.

#### 2.5.4 Confounders

Since this is an observational study and the vaccinations were not randomly assigned, confounding needs to be adjusted for in order to correctly emulate the target trials. To identify a sufficient adjustment set of confounders for each analysis we first built a directed acyclic graph (DAG), encoding our assumptions about the causal structure of the data (47). In this graph each node corresponds to one variable or concept while the directed arrows between them denote directed causal effects. The absence of an arrow between two nodes is equal to the assumption that there is no direct causal effect of one node on the other. We built this DAG primarily based on a previously suggested DAG by Stuurman et al. (48) and Remschmidt et al. (49), including additional information extracted from other relevant studies (30, 50–52) and through expert discussion. The resulting DAG is shown in Figure 1.

**Figure 1 F1:**
[figure not shown]
The assumed causal directed acyclic graph (DAG). The two vaccines of interest are drawn in green, the two main outcomes are drawn in blue and the considered confounders are drawn in red.

To make the DAG more comprehensible, we excluded the time dimension from it, even though all of the considered nodes are actually time-dependent. For the same reason we also grouped together all factors that are hypothesized to have the same causes under one concept each, as was done in Stuurman et al. (48). An explanation of each considered variable and concept, as well as a list of indicators used to represent them in the actual analysis (if necessary), is given in Table 2. The variables corresponding to the respective vaccines [*Influenza Vaccine* and *HZ Vaccine* (herpes zoster vaccine)] and the variables corresponding to the associated main outcomes [*Influenza Infection* (medically attended influenza) and *HZ Infection* (medically attended herpes zoster infection)] are not listed in Table 2, because they have been described in detail earlier.

**Table 2 T2:** A description of the variables or concepts and a list of corresponding indicators that could and/or will be used to measure them.

**Description**	**Indicator(s)**
**Age**	
The age of the patient in years.	The year of birth is used to obtain the age in years.
**Sex**	
The biological sex of the patient (male/female).	This variable is directly recorded in the BARMER database.
**Calender time**	
The date of the inclusion into the study.	This variable is also directly recorded in the BARMER database.
**Place (Place of residence)**	
The place of residence of the individual.	The first three digits of the postal code of an individual or the associated federal state will be used as a rough proxy for the place of residence.
**Soc. factors (Socioeconomic factors)**	
Socioeconomic status and ethnicity of an individual.	None available.
**HSB (Healthcare-seeking behavior)**	
Healthcare seeking behavior, defined as the individuals propensity to seek medical care when ill or perceived ill.	Although not directly observable, several indicators of HSB can be identified from the data (80). We will consider: (1) The number of primary care physician visits in the year before study entry (48). (2) The total number of visits to a physician in the year before study entry. (3) Whether the individual has received a pneumococcal vaccination in the 2 years before study entry, similar to recommendations by World Health Organization (30). (4) Whether the individual has participated in a voluntary preventive medical check-up as coded by the “Einheitliche Bewertungsmaßstab Ziffer” (EBM) number 01732 in the last 2 years.
